## VIII.2. Doses, administration modalities and duration of treatment

### VIII.2.1 Prescribing, Specification and Ratio of Dose to the VTP

A dose of 36Gy in 6 fractions delivered in 11-13 days seems to be the most appropriate regimen in this indication in terms of benefit/risk ratio (*see I.4. for details on the calculation of BEDs*). In the absence of a specific ICRU recommendation for stereotactic radiotherapy, the prescription is generally made to encompass at least 95% of the PTV in the prescribed physical dose, which in this case is 36Gy.

The dose will usually be prescribed on the usual isodose chosen with the stereotactic technique. Normalization on the maximum dose within the PTV varying with the stereotactic technique may be necessary.

Several types of prescriptions are authorized depending on the equipment and techniques of each center, in particular prescriptions such as RCMI or Cyberknife type (see below). The prescribed physical dose of PTV in the envelope is always 36Gy.

- ❖ **In RCMI type prescription** The prescription isodose of 36Gy will be 100% isodose to cover at least 95% of the PTV. The coverage of the PTV will be as homogeneous as possible due to the post-operative situation. It is recommended that 5% of the PTV (D5%) receive no more than 39.6Gy (110% of the prescribed physical dose of 36Gy) (45) and that 1cc of healthy tissue (outside the PTV) receives no more than 39.6Gy (110% of the prescribed physical dose of 36Gy).

- ❖ **As a prescription such as Cyberknife**, the prescription isodose of 36Gy will be determined to limit heterogeneities within the target volume as much as possible (classically isodose 80%) to cover at least 95% of the PTV. This implies that important heterogeneities are thus tolerated within the PTV but are not sought and should be as low as possible. The prescription must clearly measure the risk of a considerable increase in the dose delivered to a sensitive organ with a high probability of risk of complications (see Table 4 of the dose-volume objectives for planning). It is recommended that 20% of the PTV (D20%) receive no more than 39.6Gy (110% of the prescribed physical dose of 36Gy) (45) and that 1cc of healthy tissue (outside the PTV) receives no more than 39.6Gy (110% of the prescribed physical dose of 36Gy).

It should be noted that these prescription modalities are dependent on the stereotactic technique but also on the organs at risk and that the recording of deviations in terms of dose to the SROs is provided for in the protocol (see Table 4 of the dose-volume objectives for planning).

The conformance and homogeneity indexes will be reported in the eCRF.

847 **Table 4. Dose-volume objectives for planning.**

| PTV or SRO/PRV                              | D95% | D min                                 | D2%
D max                                          | D5%
D20%                                   | D avg
Average Dose | Dose/
volume                                |
|---------------------------------------------|------|---------------------------------------|-------------------------------------------------------|-----------------------------------------------|-----------------------|------------------------------------------------|
| PTV prescription RCMI                       | 36Gy | $\geq 32.4\text{Gy}$
(90% of 36Gy) | $D_{\max} \leq 45\text{Gy}$
( $\leq 25\%$ of 36Gy) | $D5\% \leq 39.6\text{ Gy}$
(110% of 36Gy)  |                       |                                                |
| PTV prescription Cyberknife                 | 36Gy | $\geq 32.4\text{Gy}$
(90% of 36Gy) | $D_{\max} \leq 45\text{Gy}$
( $\leq 25\%$ of 36Gy) | $D20\% \leq 39.6\text{ Gy}$
(110% of 36Gy) |                       |                                                |
| GRP Spinal cord                             |      |                                       | $D_{\max} \leq 18\text{ Gy}$                          |                                               |                       |                                                |
| PRV Spinal Canal                            |      |                                       | $D2\% \leq 22.5\text{ Gy}$                            |                                               |                       |                                                |
| GRP Chiasma                                 |      |                                       | $D2\% \leq 27\text{ Gy}$                              |                                               |                       |                                                |
| PRV Optic nerves                            |      |                                       | $D2\% \leq 27\text{ Gy}$                              |                                               |                       |                                                |
| GRP Brainstem                               |      |                                       | $D2\% \leq 27\text{ Gy}$                              |                                               |                       |                                                |
| CL Parotid                                  |      |                                       |                                                       |                                               | $\leq 5\text{ Gy}$    |                                                |
| HL parotid                                  |      |                                       |                                                       |                                               | $\leq 20\text{ Gy}$   |                                                |
| Mandible                                    |      |                                       | $D2\% \leq 36\text{ Gy}$
(Mandible excluding PTV)  |                                               |                       | $V29\text{Gy} < 30\%$
$V32\text{Gy} < 16\%$ |
| Supraglottic Larynx                         |      |                                       |                                                       |                                               | $\leq 28\text{ Gy}$   |                                                |
| Submandibular gland CL                      |      |                                       |                                                       |                                               | $\leq 5\text{ Gy}$    |                                                |
| Submandibular gland HL                      |      |                                       |                                                       |                                               | $\leq 26\text{ Gy}$   |                                                |
| PRV Carotid Artery HL (excluding PTV)       |      |                                       | $D2\% \leq 36\text{ Gy}$                              |                                               |                       |                                                |
| GRP Cochlea HL                              |      |                                       | $D_{\max} \leq 18\text{ Gy}$                          |                                               |                       |                                                |
| GRP Cochlea CL                              |      |                                       | $D_{\max} \leq 5\text{ Gy}$                           |                                               |                       |                                                |
| HL inner side of the cheek (excluding PTV°) |      |                                       |                                                       |                                               | $\leq 28\text{ Gy}$   |                                                |
| CL inner cheek surface                      |      |                                       |                                                       |                                               | $\leq 5\text{ Gy}$    |                                                |
| Oral cavity (excluding PTV)                 |      |                                       | $D2\% \leq 36\text{ Gy}$                              |                                               | As low as possible    |                                                |
| Pharyngeal constrictor muscle               |      |                                       |                                                       |                                               | $\leq 12\text{ Gy}$   |                                                |
| Lips                                        |      |                                       |                                                       |                                               | $\leq 5\text{ Gy}$    |                                                |

848 *HL: ipsilateral; CL: contralateral.*

849 *Doses to SROs should be kept as low as possible.*

## 850 **VIII.2.2 Spreading**

- 851 • Patients will preferably be treated with **the first fraction delivered on Monday.**
- 852 • The 6 fractions will be delivered in 11-13 days, 3 fractions per week.
- 853 • A minimum of 36 hours will be required between 2 fractions.

## 854 **VIII.2.3 Treatment Planning**

855 The stereotactic irradiation technique is left to the choice of the investigator according to the  
 856 equipment available. The arrangement of the beams, the choice of energies, the planimetry according  
 857 to the TPS, are left to the discretion of the investigators provided that they comply with the  
 858 recommendations defined in the protocol in order to obtain an optimal dose distribution. The use of  
 859 non-coplanar beams is permitted.

860 The dose-volume objectives for planning are described in Table 4.

## 861 **VIII.2.4 Time Interval Between Surgery and Stereotactic Radiotherapy**

862 The time interval between surgery of the primary tumor and the start of stereotactic radiotherapy will  
 863 be **less than 6 weeks, maximum 8 weeks.**

## 864 **VIII.2.5 Checking positioning during stereotactic radiotherapy sessions**

865 The positioning of the patients should be checked at each treatment session with an IGRT procedure  
 866 adapted according to the institutional protocol according to the technique and the anatomical location  
 867 of the volume treated. The corrections necessary for optimal repositioning will be systematically  
 868 applied.

## 869 **VIII.2.6 Interruptions or modifications of treatment**

- 870 • No changes to target volume selection and delineation, dose prescribing, or spreading will be  
 871 permitted (major deviations).
- 872 • The local investigators will take all appropriate measures to avoid any interruption and/or  
 873 modification of the total dose delivered.

874 However, it is the responsibility of the local investigator to discontinue treatment in a duly justified  
 875 manner if it is in the best interest of the patient. This interruption will be documented in the medical  
 876 record and reported in the eCRF. ***In the event of a breakdown or overhaul of the accelerator or***  
 877 ***public holidays, all measures must be taken to avoid prolonging the spread of the treatment.***

878

## 879 IX. STATISTICAL CONSIDERATIONS

880

### IX.1. Number of topics to include

881 To determine the number of patients needed, two objectives were considered: severe late toxicity at  
882 2 years (primary outcome) and local control rate at 2 years (secondary outcome). The experimental  
883 design follows a one-step Fleming design with no intermediate analysis due to the primary endpoint  
884 which will be evaluated at 2 years (severe late toxicity).

885 The safety and efficacy profile of hypofractionated stereotactic radiotherapy of the operative bed is  
886 expected to be equivalent to other radiotherapy techniques (brachytherapy or normofractionated  
887 IMRT) (cf 3. Rationale of the study for details). In brachytherapy, the rate of late soft tissue ulceration  
888 is around 10-20% and the rate of bone necrosis is around 5-10%. We have decided: 1/ to accept a rate  
889 of less than 5% and 2/ to reject a rate of more than 15%. With a unilateral test for significance ( $\alpha=0.05$ )  
890 with a power of 90% ( $\beta=0.10$ ), the minimum number of patients to be included is 67.  
891 Hypofractionated stereotactic radiotherapy of the operative bed will then be considered an  
892 unacceptable treatment if 6/67 patients (9%) or more have severe late toxicity (grade  $\geq 3$ ).

893 The local control rate of hypofractionated stereotactic radiotherapy is expected to be equivalent to  
894 other radiotherapy techniques (brachytherapy or normofractionated IMRT). We have decided: (i) to  
895 accept a rate of more than 90% and (ii) to reject a rate of less than 80%. With a one-sided significance  
896 test ( $\alpha=0.05$ ) with a power of 80% ( $\beta=0.20$ ), the minimum number of patients to be included is 83.  
897 A lower potency was decided for control as a secondary outcome. Hypofractionated stereotactic  
898 radiotherapy of the operative bed will then be considered an acceptable treatment if 72/83 patients  
899 (87%) or more are locally controlled at 2 years.

900 As a result of these results, and to compensate for possible loss to follow-up, a total of 90 patients  
901 will be included in this study.

902 As the primary objective of this study is estimated at 2 years, once 30 patients have been included  
903 (33% of inclusions), a review of all grade  $\geq 3$  toxicities will be communicated to the independent trial  
904 monitoring committee (IDSMC = *Independent Data and Safety Monitoring Committee*). The grade 4  
905 toxicity rate is expected to be less than 10%. Inclusions will not be stopped during this evaluation.

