### IV. RESEARCH DESIGN

#### IV.1. Primary endpoint

**Rate of patients with late toxicity at 2 years grade  $\geq 3$**  according to the NCI - CTCAE V4.03 classification in connection with hypofractionated stereotactic radiotherapy, i.e. grade  $\geq 3$  toxicities occurring beyond 3 months after the end of stereotactic radiotherapy.

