### V.3.3 Discontinuation of the study

The end of the study is expected when the last patient has completed their follow-up at 2 years. The study may be stopped prematurely if the toxicity is too high or the inclusion rate is too low. The independent oversight committee will make its recommendations. It is the developer who will decide on the stoppage.

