## VI. RESEARCH METHODOLOGY

### VI.1. Description of the research methodology

This is a multicenter, national, non-randomized, phase 2, open-label trial that aims to evaluate the toxicity and efficacy profile of hypofractionated stereotactic radiotherapy of the operative bed of localized cancers of the oral cavity and oropharynx with risk margins. The experimental design was chosen according to a Fleming design at one stage without intermediate analysis because of the primary endpoint which will be evaluated at 2 years (severe late toxicity).

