### 535 ***VI.5.1 Assessment during immediate follow-up visits***

#### 536 **Follow-up visit at 14±3 days after the last stereotactic radiation therapy session**

- 537 • Clinical examination including weight  
 538 • Assessment of general condition according to WHO status  
 539 • Tumor bed examination (clinical +/- nasofibroscopy)  
 540 • Examination of the mouth, throat and neck

- 541 • Type of feed (Solid, liquid, mixed...)
- 542 • Acute toxicity assessments according to NCI-CTCAE v.4.03
- 543 • Collection of concomitant treatments

544

545 **Follow-up visit at 30±5 days after the last stereotactic radiotherapy session**

- 546 • Clinical examination including weight
- 547 • Assessment of general condition according to WHO status
- 548 • Tumor bed examination (clinical +/- nasofibroscopy)
- 549 • Examination of the mouth, throat and neck
- 550 • Type of feed (solid, liquid, mixed, etc.)
- 551 • Acute toxicity assessments according to NCI-CTCAE v.4.03
- 552 • Collection of concomitant treatments
- 553 • EORTC QLQ-C30 and H&N35 Questionnaire

554

555 **Follow-up at 3 months ±10 days after the last stereotactic radiation therapy session**

- 556 • Clinical examination including weight
- 557 • Assessment of general condition according to WHO status
- 558 • Tumor bed examination (clinical +/- nasofibroscopy)
- 559 • Examination of the mouth, throat and neck
- 560 • Type of feed (solid, liquid, mixed, etc.)
- 561 • Acute toxicity assessments according to NCI-CTCAE v.4.03
- 562 • Carcinologic evaluation:
  - 563 ❖ CT scan or cervicofacial MRI (*The choice between MRI and CT is left to the*
  - 564 *discretion of the investigator but follow-ups must be carried out with the same*
  - 565 *technique)*
  - 566 ❖ Chest CT scan (*The use of PET-FDG is left to the choice of the investigators in each*
  - 567 *center if it is medically indicated)*

568

569

570 **VI.5.2 Assessment during long-term monitoring visits**

571 These visits will take place every **3 months±10 days for up to 2 years** after stereotactic radiotherapy

572 and include:

- 573 • Clinical examination including weight
- 574 • Assessment of general condition according to WHO status
- 575 • Tumor bed examination (clinical +/- nasofibroscopy)

- 576 • Examination of the mouth, throat and neck
- 577 • Type of feed (solid, liquid, mixed, etc.)
- 578 • Late toxicity assessments according to NCI-CTCAE v.4.03
- 579 • Carcinologic assessment at **12 months and 24 months**

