### 933 **IX.3. Main analysis**

934 The analysis of the main objective, i.e. the rate of severe toxicity of grade  $\geq 3$  to 2 years, with its 95%  
 935 CI will be compared to 15% (with regard to the assumptions set in the context of the estimation of  
 936 the number of subjects needed). If the 95% CI does not include this rate, the trial will be considered  
 937 positive. For efficacy endpoints, 95% bilateral confidence intervals will be provided. Statistical  
 938 analysis will be performed on an intention-to-treat basis.

939 An analysis of the predictive factors of severe toxicity of grade  $\geq 3$  to 2 years will be performed. A  
 940 univariate analysis will be performed using the usual tests: Student's test or Mann-Whitney test if the  
 941 conditions of the t-test are not met (normality, and homoscedasticity studied by the Fisher-Snedecor  
 942 test) for quantitative variables and Chi2 test or Fisher's exact test for categorical variables. The  
 943 multivariate analysis will consider a logistic regression model for binary dependent variable.  
 944 Covariates will be retained based on the results of univariate analysis and their clinical relevance.

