## X. INDEPENDENT OVERSIGHT COMMITTEE

The *Independent Data and Safety Monitoring Committee (IDSMC)* will conduct a review of all safety data from the trial and all events identified as requiring potential advice. It will be composed of 3 experts: 2 radiotherapists and 1 statistician/methodologist. The experts conducting this review will be selected for their expertise in clinical research and in the field of the study and will conduct an independent review. The IDSMC may propose modifications to the protocol (eligibility criteria, dose, etc.), premature termination of the trial, etc. Its opinion is advisory to the Promoter, who is responsible for making the final decision on the implementation of the recommendations proposed by this committee.

Since the primary objective of this study is evaluated at 2 years, once 30 patients have been included (33% of inclusions), a review of all grade  $\geq 3$  toxicities will be reported to the IDSMC. The grade 4 toxicity rate is expected to be less than 10%. Inclusions will not be stopped during this evaluation.

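### The safety oversight has no number tied to the primary event: the one scheduled review comes too early to see late grade ≥3 toxicity, and its only figure concerns grade 4

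*Protocol*

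**What the plan says.** **Design.** Protocol VI.1 describes a Fleming "design at one stage without intermediate analysis because of the primary endpoint" being evaluated at 2 years. IX.1 gives the same reason: the "design follows a one-step Fleming design with no intermediate analysis due to the primary endpoint" falls at 2 years. The toxicity part sets 5% against 15%, with N = 67 and a final cut-off of 6/67. In total 90 patients are included over 48 months.

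**Endpoint and visits.** Section IV.1 counts treatment-related grade ≥3 "toxicities occurring beyond 3 months after the end of stereotactic radiotherapy". Section VI.5.2 schedules visits every 3 months up to 2 years, with "Late toxicity assessments according to NCI-CTCAE v.4.03" at each.

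**Success criterion.** IX.3 compares the rate and its 95% confidence interval with 15%: "If the 95% CI does not include this rate, the trial will be considered" positive. The interval method is not named.

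**Oversight.** IX.1 and X send all grade ≥3 toxicities to the independent committee (IDSMC) once 30 patients are included. The figure attached is: "The grade 4 toxicity rate is expected to be less than 10" percent. IX.1 adds: "Inclusions will not be stopped during this evaluation". Section X gives the committee an advisory remit over all safety data, including proposing termination. Section V.3.3 says: "The study may be stopped prematurely if the toxicity is too high or the inclusion rate is too low".

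**The concern.** The stated reason works in one direction only. Success cannot be declared before patients have been followed to 2 years. Failure can be, because a confirmed late grade ≥3 event is not undone by longer follow-up. With 48 months of accrual and quarterly grading, the count can pass the point where the IX.3 criterion is out of reach while patients are still being included.

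The protocol itself fixes the review time and the review figure, and neither suits the primary endpoint. At 30 inclusions few patients have reached a late-toxicity visit. The grade 4 figure concerns another grade, is not limited to late events and has no action attached. The stop clause in V.3.3 gives no number. At stake is whether the committee is prompted to look at continued inclusion once a positive result is no longer possible.

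**Working it through.** **1. The plan's own figure.** One-stage normal approximation, with inputs from IX.1 (5% vs 15%, one-sided α = 0.05, power 90%):

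N = [1.645·√(0.05·0.95) + 1.282·√(0.15·0.85)]² / 0.10² = (0.358 + 0.458)² / 0.01 = 66.6, so 67. This reproduces.

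**2. When a positive result becomes impossible with n = 90.** IX.3 is read as requiring the upper limit to lie below 15%. The exact upper limit is the 1−a quantile of Beta(x+1, n−x), with a = 0.025 (two-sided 95%) or 0.05 (one-sided).

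| Events of 90 | Exact two-sided | Wilson | Exact one-sided | Wald |
|---|---|---|---|---|
| 6 | 13.9% | 13.8% | 12.7% | 11.8% |
| 7 | **15.4%** | **15.2%** | 14.1% | 13.3% |
| 8 | 16.8% | 16.6% | **15.5%** | 14.8% |
| 9 | 18.1% | 17.9% | 16.8% | **16.2%** |

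The first count that closes off success is 7, 7, 8 or 9 by method. Fewer evaluable patients only raise the limit (exact two-sided, 7/83: 16.6%). A count of 6, taken from the 6/67 rule, would be too early with 90 patients.

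**3. What the 30-inclusion review can see.** With even accrual (90/48 = 1.875 per month) it falls at about month 16. Assume 1 month from inclusion to the end of radiotherapy, onset uniform over months 3-24, and detection at the next visit. By hand:
- past the 6-month visit: (16−1−6)·1.875 = 16.9 patients
- past the 9-month visit: (16−1−9)·1.875 = 11.3
- past the 12-month visit: (16−1−12)·1.875 = 5.6

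Each 3-month step reveals 3/21 = 1/7 of the events. At a true 15% the expected count is 0.15·(16.9 + 11.3 + 5.6)/7 = 0.72. Simulation gives 0.70.

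Over eight assumed settings (onset uniform or late-skewed, accrual uniform or linearly rising, loss 0% or 25% by 24 months), the mean is 0.2-1.0 late events, and 38-86% of trials show none. With rising accrual the review falls near month 27. In either case about 16 of the 30 patients have passed the 6-month visit, 5-8 the 12-month visit, and almost none the 24-month visit.

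**4. How often the count is reached before the last inclusion.** Simulation of 20,000 trials per setting: inclusion times uniform on 0-48 months or 48·√U; onset U(3,24) or 3 + 21·Beta(3,1.5) months; visits at 6, 9, …, 24 months; exponential loss. Each cell is the range over the eight settings: chance of reaching the count, then mean patients included afterwards (0 if never reached).

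| True rate | Count 7 | Count 8 | Count 9 |
|---|---|---|---|
| 15% | 9-79% (1-16) | 4-67% (0.4-11) | 2-53% (0.1-8) |
| 20% | 27-96% (3-25) | 15-92% (2-21) | 7-85% (0.7-16) |
| 30% | 67->99% (12-37) | 53->99% (8-34) | 38->99% (5-30) |

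For count 7 at lower true rates: 0-3% at 5%, and 2-38% (0.2-5 patients) at 10%. A rerun for this write-up agreed within simulation error.

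**The case against.** A one-stage design without an interim analysis is legitimate, its reason is stated, and committee triggers are often kept in a charter, which is not shown here. This stands in part. The design needs no change, and if a charter already holds a number a cross-reference is enough. But the protocol does set a review time and a review figure, and these cannot pick up failure on its own primary endpoint.

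Four stronger readings are tempting, and the documents do not support them.
- **That there is no failure signal at all.** The committee's remit covers all safety data, it may propose termination, it receives every grade ≥3 toxicity at 30 inclusions, and V.3.3 allows a stop. What is missing is a number.
- **That the expected late rates in XI.1.3 are oversight limits set too loosely.** They define which reactions count as expected. They carry no grade, so they cannot be set against the 15% limit.
- **That grade 3 events not classed as serious escape oversight.** XI.2.2 puts them in the case report form, and they are safety data under section X.
- **That reaching the count shows harm.** Seven of 90 is 7.8%. IX.1 quotes 10-20% soft tissue ulceration and 5-10% bone necrosis for brachytherapy. The count shows only that 15% cannot be excluded. Continuing inclusion for local control, quality of life and toxicity predictors can be defended.

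The size of the benefit also rests on inputs the protocol does not give. With rising accrual, 25% loss and a true 15%, only 1-4 patients on average are included after count 7. Time to confirm relatedness, which the simulation leaves out, would reduce this further.

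**Conclusion.** The point holds in a limited form. The 2-year endpoint justifies having no early look for success, but the oversight contains no quantitative signal tied to the primary event, and the scheduled review cannot supply one (0.2-1.0 expected late events at a true 15%).

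The practical size ranges from negligible to material. For count 7, a mean of about 1-16 patients would be included after success is out of reach at a true 15%, and 12-37 at a true 30%. These figures depend on assumed onset, accrual shape and loss. Recurrence, which ends toxicity follow-up under VI.5.3, is represented only through the loss settings. The trigger number depends on the interval method that IX.3 leaves open. It is an inexpensive improvement to consider, and the design itself is sound on this point.

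**What to change.** Keep the one-stage design and the 30-patient review. First name the interval method in IX.3 and reconcile it with the 6/67 cut-off. Then add to IX.1, V.3.3 and X:
- The IDSMC is convened promptly when the running number of patients with late grade ≥3 toxicity, confirmed as treatment-related, reaches the smallest count at which IX.3 cannot be met with 90 patients: 7 (exact or Wilson two-sided 95%), 8 (exact one-sided 5%) or 9 (Wald).
- Only confirmed events count, because under XI.2.4 the sponsor also decides imputability and an unconfirmed count could fall.
- The committee advises on continuing, pausing or stopping inclusion, and the sponsor decides. Inclusion does not stop automatically, and treated patients stay in planned follow-up.

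**Cost.** Amendment wording, a running count from the existing electronic case report form, confirmation of relatedness for a handful of events, and at most one extra committee meeting. No visits are added. No type I error or primary power is spent, since the trigger fires only when a positive result is already impossible.

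**Downside.** At a true 10%, count 7 would convene the committee during accrual in about 2-38% of trials. If inclusion were then stopped, late toxicity, its predictors and the 72/83 local control rule would rest on fewer patients. That is why the trigger is advisory.

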## STATISTICAL CONSIDERATIONS

### Estimating the number of patients needed

With a one-step Fleming plan, the calculation of the number of patients needed takes into account:

- The primary endpoint: severe toxicity at 2 years limited to 5-15%, minimum N is equal to 67 patients (unilateral,  $\alpha = 0.05$ ,  $\beta=0.10$ )
- and the secondary endpoint: 2-year local control of 80-90%, minimum N is equal to 83 patients (unilateral,  $\alpha = 0.05$ ,  $\beta=0.20$ )

In order to compensate for possible loss to follow-up, 90 patients will be included.

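### The primary-endpoint figures 67 and 6/67 do not fit together at one-sided alpha 0.05 and 90% power, and neither fits the two-sided 95% CI test against 15% in IX.3

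*Protocol*

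**What the plan says.** Protocol IX.1 describes a single-stage Fleming design ("design follows a one-step Fleming design with no intermediate analysis due to the primary endpoint"). It accepts a severe late toxicity rate "of less than 5% and 2/ to reject a rate of more than 15" per cent. The error rates are set "With a unilateral test for significance" at alpha 0.05 and "with a power of 90" per cent. From these, "the minimum number of patients to be included is 67"; the synopsis repeats this ("minimum N is equal to 67 patients"). The decision rule is to call the treatment an "unacceptable treatment if 6/67 patients (9%) or more have severe late toxicity". No rate is named as the null hypothesis.

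IX.3 estimates the rate with a 95% CI. That "CI will be compared to 15% (with regard to the assumptions set in the context of the estimation of" the sample size), and the trial is positive if the interval excludes 15%. IX.2 says that tests are two-sided.

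For local control, IX.1 gives 83 patients (80% against 90%, one-sided 0.05, power 80%). Total enrolment is 90, to allow for loss to follow-up.

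**The concern.** In a single-arm toxicity design the choice of null decides which mistake is held at 5%. With 5% as the null, alpha is the risk of condemning a safe treatment, and the 10% beta is the risk of passing one with 15% severe toxicity. With 15% as the null, the two are exchanged. The sample size appears to use the first arrangement and the analysis the second, although IX.3 refers back to the sizing assumptions as if they were the same. A cut-off that belongs to neither, and a CI rule at a different error level, would leave the primary safety decision without known error rates. Two sections could also give different answers on the same data.

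**Working it through.** **Inputs.** From IX.1: rates 5% and 15%, one-sided alpha 0.05 (z = 1.645), power 90% (z = 1.2816), N = 67, unacceptable at 6 or more. From IX.3: two-sided 95% CI against 15%.

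**Sample size.** Fleming normal approximation: n = [(z_alpha·√(p0·q0) + z_beta·√(p1·q1)) / |p1 − p0|]², with √(0.05×0.95) = 0.2179 and √(0.15×0.85) = 0.3571.

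- Null 5%: [(1.645×0.2179 + 1.2816×0.3571)/0.10]² = 66.6, so 67. This reproduces the plan's figure.
- Null 15%: [(1.645×0.3571 + 1.2816×0.2179)/0.10]² = 75.1, so 76. The smallest exact binomial design is also 76, acceptable at 6 or fewer: alpha 4.97%, power 91.4%.

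Local control is sized the other way round. With z = 0.8416 for 80% power, the formula gives 82.9 (83, as stated) with the unacceptable rate of 80% as the null, and 68.9 with 90% as the null. Within IX.1, efficacy is thus sized against the unacceptable rate and toxicity against the acceptable one.

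**Cut-off at 67.** Approximate boundaries:

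- Null 5%: 67×0.05 + 1.645×√(67×0.05×0.95) = 3.35 + 1.645×1.784 = 6.28, so rejection starts at 7.
- Null 15%: 67×0.15 − 1.645×√(67×0.15×0.85) = 10.05 − 1.645×2.923 = 5.24, so at most 5 is acceptable and 6 is unacceptable.

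Exact binomial errors:

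| Rule | Null | Alpha | Power |
|---|---|---|---|
| Unacceptable if ≥6/67 (as stated) | 5% | 11.8% | 94.9% |
| Unacceptable if ≥7/67 | 5% | 4.97% | 89.3% |
| Acceptable if ≤5/67 (as stated) | 15% | 5.1% | 88.2% |
| Acceptable if ≤4/67 | 15% | 2.0% | 75.7% |

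So 67 fits a null of 5%, and the cut-off of 6 fits the approximate boundary for a null of 15%.

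**IX.1 against IX.3.** At 5/67 the exact (Clopper-Pearson) two-sided 95% upper limit is 16.6%; at 4/67 it is 14.6%. Five events are therefore not unacceptable under IX.1 and not positive under IX.3. With an exact interval, 67 patients need at most 4 events, and power at a true rate of 5% is 75.7%. A Wald interval at 5/67 ends at 13.8% and would agree with IX.1. The protocol does not name the interval.

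**At the numbers likely to be analysed** (null 15%, alternative 5%):

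| Evaluable | One-sided 0.05, exact | Two-sided 95% CI, exact |
|---|---|---|
| 90 | ≤7: alpha 3.1%, power 91.9% | ≤6: alpha 1.3%, power 83.6% |
| 83 | ≤6: alpha 2.6%, power 87.8% | ≤5: alpha 1.0%, power 76.5% |

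The cut-off must follow the evaluable number: 7 events in 83 would have alpha 5.7%. At 7/90 the exact two-sided 95% upper limit is 15.4%, so a 7/90 rule also conflicts with IX.3 as it stands.

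**The case against.** The strongest defence is that the error that matters to patients is almost intact. IX.1 says that a rate above 15% is to be rejected, and IX.3 tests against 15%. On that reading the stated rule has alpha 5.1% and power 88.2%: 0.1 point over and 1.8 points under. That is ordinary discreteness for a design sized by a normal approximation, and the protocol does not promise an exact design. This stands.

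A reader might take the 11.8% to mean that toxic treatment is likely to be passed. It does not mean that. It is the chance of condemning a treatment whose true rate is 5%. Compared with 7/67, the stated cut-off is the stricter safety rule: it passes a 15% rate with probability 5.1% instead of 10.7%.

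A reader might also infer that the trial is too small. The documents do not support that for the one-sided design. The corrected minimum of 76 lies below both the 83 for local control and the planned 90.

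Finally, the null of 5% is an inference from the formula, because IX.1 names none. This stands too, but it does not rescue the figures. No choice of null gives 67, a cut-off of 6 and the stated errors together. The gap between a one-sided 0.05 test and a two-sided 95% CI is in the text whichever null is meant.

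**Conclusion.** The inconsistency is real and of moderate weight. The figure 67 comes from a null of 5%, while the analysis uses 15%, which needs 76. The 6/67 rule misses the stated alpha badly if 5% is the null (11.8%) and only slightly if 15% is the null (5.1%, power 88.2%). Under an exact interval, IX.1 and IX.3 disagree at 5/67.

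The binomial figures assume independent patients, all evaluable at 2 years. The 75.7%, 76.5% and 83.6% powers also assume an exact interval. The protocol does not specify one, so they should not be read as the plan's stated power.

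What remains open is which error is held at 5% and which rule decides when the two sections differ. Neither point calls for more patients at one-sided 0.05. If the exact two-sided 95% CI is kept, the smallest design with 90% power is 93 (acceptable at 7 or fewer: alpha 2.35%, power 90.6%), slightly above 90.

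**What to change.** Keep enrolment at 90 and change the text of the synopsis, IX.1 and IX.3:

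1. Name 15% as the null and 5% as the alternative.
2. Replace 67 by 76 as the minimum for the primary endpoint.
3. Use one error level in both sections. One-sided 0.05 corresponds to a two-sided 90% CI, or a one-sided 95% upper bound, in IX.3. If the two-sided 95% CI stays, restate the power. In either case name the interval method.
4. Replace 6/67 by a cut-off defined for the number of evaluable patients: the largest count that meets the chosen error level against 15%. The working gives the values for 90 and 83 evaluable patients under both choices. At one-sided 0.05, exact power is below 90% at 83 evaluable but at least 90% from 85 upwards.

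The cost is an amendment of wording and figures before the database is frozen, with the analysis plan aligned to it. No patients, visits or recruitment time are added.
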